Due to all these limitations, there are no adequately established reference values (RVs) for nutrient concentrations in milk, and recommended nutrient intakes of infants, young children, and lactating women are based on many unvalidated and incorrect estimates of milk MN concentrations. Given the lack of RVs there is no benchmark against which to evaluate human milk quality in different populations, or the possible need for or effects of nutrient interventions on human milk MNs.

The primary study outcome and analysis objective of the Mothers, Infants, and Lactation Quality (MILQ) Study is the construction of reference ranges for values of vitamin and mineral concentrations in human milk from well-nourished mothers and their healthy infants. The reference range curves, between the 2.5 and 97.5 percentiles, will be constructed between 1 and 8.5 mo by combining data from the 4 study sites, using nutrient and volume data from milk samples obtained from each mother during 3 visits postpartum. This article describes the methodologies and protocols implemented for conducting the MILQ Study.

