#### Establishing equivalency among study sites

For each nutrient and time period, pairwise comparisons using the 2, 1-sided test (TOST) method will be used to compare the means of the 4 sites for equivalence (20). If differences >0.3 SD are detected, a follow-up test will be conducted to compare each mean to the combined means of the other 3 sites, to determine which sites can be pooled. A sample size of 200 per site in each time period is sufficient to detect differences of 0.25 SD with 80% power or differences of 0.30 SD with 90% power. Therefore, the planned sample size of 250 per site and time period will provide adequate power to determine whether 1 site is different from the others (**Table 5**).

**TABLE 5 tbl5:** Required sample sizes for testing equivalence

Differences (site means)	Sample size/site 80% power	Sample size/site 80% power
0.20 SD	310	429
0.25 SD	199	275
0.30 SD	139	191

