**FIGURE 3 fig3:**
[figure not shown]
Hypothetical graphical illustration of reference values that may result for a micronutrient.

For each nutrient and time period, the distribution of the human milk variable will be examined and extreme outliers will be investigated and, if needed, removed. Box–Cox and other transformations will be used to normalize each variable, preferably using the same transformation across study sites, and the Shapiro–Wilk statistic to assess normality; skewness, kurtosis. The general shape of the distribution will also be examined. Parameters will be compared among study sites as described above, and information from the sites will be combined if the sites are deemed to be equivalent, or if differences have no material effect on key percentiles; otherwise, different sets of RV centiles may be constructed per site, or with only 2 or 3 pooled sites.

Parameters from the identified distribution will be estimated from the data, and centiles of interest (5th, 25th, 50th, 75th, 95th) will be estimated for each nutrient based on the theoretical percentiles of the underlying distribution, as described above. Smoothing techniques such as cubic splines will be employed, assuming the centiles follow smooth and continuous functions. Tables and curves of estimated centiles will be created for each nutrient and time period. SAS for Windows Release 9.4 (SAS Institute) will be used for all analyses.

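### The stated 80%/90% power is for one pair of sites, while the first pooling step runs six pairwise equivalence tests; identical sites pass all six about 68% of the time at 250 per site

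*Protocol article*

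**What the plan says.** The Introduction gives the primary objective as reference range curves constructed "by combining data from the 4 study sites". The sample size section names establishing equivalency before pooling as one of its two bases.

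Under Establishing equivalency among study sites, the first step is repeated by nutrient and by visit window: "pairwise comparisons using the 2, 1-sided test (TOST) method will be used to compare the means of the 4 sites for equivalence". A second step is conditional: "If differences >0.3 SD are detected, a follow-up test will be conducted to compare each mean to the combined means of the other 3 sites", and its purpose is "to determine which sites can be pooled".

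The power statement is that "A sample size of 200 per site in each time period is sufficient to detect differences of 0.25 SD with 80% power", or 0.30 SD with 90%. From this the article concludes that "the planned sample size of 250 per site and time period will provide adequate power to determine whether 1 site is different from the others". The accompanying Table 5 lists 310, 199 and 139 per site in one column and 429, 275 and 191 in the other, for 0.20, 0.25 and 0.30 SD. Both columns are headed 80% power.

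The Data analysis plan says that "information from the sites will be combined if the sites are deemed to be equivalent". The same sentence also allows combination where differences do not materially change the key percentiles, and otherwise allows site-specific centiles or pooling of two or three sites.

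No significance level is given, and no power for the six comparisons taken together.

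**The concern.** Four sites make six pairs. For the pairwise step to support pooling all four, every one of the six TOSTs has to succeed, and that is less likely than success in any one of them. A power figure for one pair therefore overstates how often the screen is passed.

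The follow-up step is worded as a response to differences being detected. A reader who believes the screen has 80% to 90% power may take a failed pair as evidence that sites differ, when with identical sites it would often be a chance failure to demonstrate equivalence. At stake is how the primary product is read: one reference range from four sites, or several partial ones.

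**Working it through.** **Inputs from the article.** Four sites, so 4 × 3 / 2 = 6 pairs; 200 and 250 per site and period; 0.3 SD as the threshold; the Table 5 figures.

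**Assumptions not in the article.** Alpha 0.05 per one-sided test; 0.30 SD as the TOST margin; common known SD, set to 1; all 250 evaluable.

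**1. Reproduce the printed figures.** A two-sample, one-sided 5% t-test for one pair gives 310/199/139 at 80% power and 429/275/191 at 90%. All six Table 5 entries match, so the second column is the 90% one. A two-sided test would give 393/252/175 at 80%, which does not match. At 200 per site the one-sided difference test has power 0.804 at 0.25 SD and 0.912 at 0.30 SD, which are the 80% and 90% in the text. The printed numbers are thus one-pair power to detect a difference.

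**2. TOST power for one pair, true difference zero.** SE = √(2/n). The pair passes if the observed difference is within c = 0.30 − 1.645 × SE, so power = 2Φ(c/SE) − 1.
- n = 200: SE = 0.1000, c = 0.1355, power 82.5%.
- n = 250: SE = 0.0894, c = 0.1529, power 91.3%.

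**3. All six pairs.** All six pass exactly when the largest site mean minus the smallest is below c. With equal true means, the probability is that of the range of four standard normals falling below c√n.
- n = 200: c√n = 1.916, probability 47%.
- n = 250: c√n = 2.417, probability 68%.

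Simulation with 1,000,000 runs agrees. With one site truly 0.10 SD away, simulation gives 30% at 200 and 44% at 250. With identical sites, 80% and 90% for all six need about 291 and 345 per site.

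**4. Add the follow-up.** Each site is compared with the other three combined, SE = √(1/n + 1/(3n)) = 0.0730 at n = 250. The article does not say which test or margin applies, so two versions were simulated at 250 per site.

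| Situation at 250 per site | Passes all six TOSTs | All four pooled after follow-up |
|---|---|---|
| Identical sites, follow-up by TOST at 0.30 SD | 68% | 95% |
| One site 0.10 SD away, follow-up by TOST at 0.30 SD | 44% | 82% |
| Identical sites, follow-up by two-sided 5% difference test | 68% | 83% |

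At 200 per site with identical sites, the TOST version pools all four about 86% of the time.

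**5. Other reading of the trigger.** If detection means an observed difference above 0.3 SD, the follow-up is reached when the range exceeds 0.30, that is 0.30 × √250 = 4.74 on the standard scale. For identical sites this happens about 0.4% of the time. That rule is not a TOST, and the printed power does not describe it either.

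**6. The one-versus-three contrast.** For a two-sided 5% difference test at 250 per site, 0.25/0.0730 − 1.96 = 1.46, so power is about 93% at 0.25 SD.

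**The case against.** The strongest reply is that the six-pair screen is not the pooling rule. A reader might infer from the 68% that identical sites would be pooled only about two times in three, or that one nutrient-period in three would be refused pooling. The article does not support this. It gives the decision on which sites to pool to the follow-up comparison, and the Data analysis plan adds a route for differences that do not matter for the key percentiles. Identical sites are the likeliest to qualify by that route. Under either version of the follow-up in the working, four-site pooling of identical sites is well above 68%. This reply stands in full, and the 68% must be read only as a first-stage pass rate.

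It is also fair that the adequate-power sentence speaks of whether one site differs from the others, which is the follow-up contrast. Step 6 shows that it is defensible there, so it needs limiting, not deleting. Pooling of fewer sites and site-specific values are foreseen outcomes, and a condensed article may leave the follow-up's test and margin to the full plan.

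None of this rescues the printed figures as a description of the screen. The article applies TOST to all six pairs and then offers one-pair figures as its power. That is a stated number attached to the wrong procedure, not an omitted detail.

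**Conclusion.** The concern holds for the first stage only. The 80%/90% statement and Table 5 are one-pair figures, and they do not give the power of the six-test screen. For identical sites that screen is passed about 47% of the time at 200 per site and 68% at 250, and 44% of the time at 250 if one site is 0.10 SD away, a shift well inside the margin. Pooling would therefore often rest on the follow-up, whose test, margin and power the article does not give. Depending on how the rule is read, identical sites at 250 are pooled about 83% or 95% of the time, or almost never reach the follow-up at all; the printed figures correspond to none of these.

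The result rests on the assumptions listed in the working. At 2.5% per one-sided test, the pass rate for identical sites at 250 falls to about 50%.

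**What to change.** In the section on equivalency among sites and in Table 5:

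1. Label the existing figures as power for one pair of sites.
2. Add the probability that all six TOSTs pass at 250 per site: about 68% for identical sites and 44% with one site 0.10 SD away, with alpha and margin stated.
3. Name the test and margin used in the follow-up, say what triggers it, and give the power of the full two-stage decision under them.
4. Limit the adequate-power sentence to the one-versus-three contrast.
5. State that a failed pairwise TOST is inconclusive and is not a detected site difference, and report the six confidence intervals with each pooling decision.

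This is wording and a small addition to one table. It needs no further participants or data. The cost is a less favourable stated figure for the first stage.

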#### Sample size estimates for other analyses

For some secondary outcome variables, e.g. free amino acids (FAA) in infant plasma, a complete sample set for analyses is not feasible or available. In such cases, only 100 samples for each site and time point are analyzed, assuming a priori that the values are similar enough to pool between ≥2 of the sites. If this is not possible, within-site percentiles will be presented with a caveat that these should not be considered as RVs, as precision is limited. However, 100 per time point is ample for looking at relations between secondary outcome variables and other outcomes, such as growth. Nevertheless, banked samples are available if initial data analyses show that analysis of >100 samples per point is needed.

Future exploratory analyses will also assess the relations between milk nutrient concentrations and other collected information, including milk volume, child growth, child developmental milestones, and maternal and infant plasma values. A sample size of 140 paired data points per site and time period is adequate to detect a correlation between continuous variables of 0.30 or higher with 95% power within each site, assuming a 2-sided alternative hypothesis, and therefore the planned sample size of 250 per site and time point is more than sufficient for these analyses.

#### Data analysis plan

The measured human milk nutrient concentrations and milk volume will be used to estimate daily nutrient intakes of the infants. The RVs will be based on these infant nutrient intakes, and developed and expressed as percentiles in these well-nourished, but nonsupplemented, population groups, following the principles used by the Intergrowth-21st Project (21), which are based on methods developed in the construction of the WHO Child Growth Standards (22) (illustrated in **Figure 3**). Criteria will be created for normal growth and development, and adequate nutritional status for each nutrient in question. Data from children who do not meet these criteria will be removed from the construction of the RVs.

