## Abstract

Little valid information is available on human milk nutrient concentrations, especially for micronutrients (MNs), and there are no valid reference values (RVs) across lactation. In this multi-center collaborative study, RVs will be established for human milk nutrients across the first 8.5 mo postpartum. Well-nourished, unsupplemented women in Bangladesh, Brazil, Denmark, and The Gambia (*n* = 250/site) were recruited during the third trimester of pregnancy. Milk, blood, saliva, urine, and stool samples from mothers and their infants are collected identically at 3 visits (1–3.49, 3.5–5.99, 6.0–8.49 mo postpartum). Milk analyses include macronutrients, selected vitamins, trace elements and minerals, iodine, metabolomics, amino acids, human milk oligosaccharides, and bioactive peptides. We measure milk volume; maternal and infant diets, anthropometry, and morbidity; infant development, maternal genome, and the infant and maternal microbiome. RVs will be constructed based on methods for the WHO Child Growth Standards and the Intergrowth-21st Project. This trial was registered at clinical trials.gov as NCT03254329.

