### Inclusion criteria

Participant's inclusion and exclusion criteria vary across the study periods but are focused mainly on the nutritional status and health of the mother and infant, and the requirement for EBF during the first 3.5 mo postpartum. Detailed information about the inclusion and exclusion criteria are provided in **Table 3**.

**TABLE 3 tbl3:** Inclusion and exclusion criteria in the Mothers, Infants, and Lactation Quality (MILQ) Study

	Bangladesh	Brazil	Denmark	The Gambia
Recruitment	Directly by local research team	Invitation letter to meet	Directly by local research team	
Enrollment	After delivery		During pregnancy	
*Mothers inclusion criteria*				
Age, y	18–40			
Height, cm	>145	≥150		
BMI, kg/m^2^				
<2 wk postpartum	≥18.5 to ≤30.0	_	_	≥18.5 to ≤30.0
Prepregnancy		≥18.5 to ≤30.0	≥18.5 to ≤30.0	
MUAC, cm	≥23 to ≤ 33	_	_	≥23 to ≤33
Hemoglobin,^1^ g/L	>100	>100	No reported anemia	>100
Maternal health	No relevant past or current medical problems (e.g. gestational diabetes, pre-eclampsia)			
Smoking	No	No	No	No
Alcohol intake, mL	<50	<40	<50	<50
Diet^2^	Nonvegan or macrobiotic diet			
	≥15 g of ≥15 food groups each/d	≥15 g of 4 of 8 food groups/d	≥15 g of ≥15 food groups each/d	
MMN use				
3rd trimester	Iron and folic acid			
			Vitamin D and calcium	
lactation	Iron and folic acid			
			Vitamin D and calcium	
Fortified foods	Low habitual intake of highly fortified foods, expect iodized salt			
Delivery	Singleton			
Weeks of gestation	37–42			
Breastfeeding				
≤3.5 mo	Exclusive breastfeeding			
≤8.5 mo	Partially breastfeeding			
Infant inclusion criteria				
Birthweight, g	2500–4200			
Infant health	No congenital malformations that interfere with feeding or growth and development			
Visit 2 exclusion criteria	Cessation of, or nonexclusive, breastfeeding			
	Serious maternal illness			
	Infant length-, weight-for-age, or weight-for-length <-2 Z			
	Maternal MMN consumption during lactation other than stated above			
Visits 3 and 4 exclusion criteria	Cessation of breastfeeding			
	Infant length-, weight-for-age, or weight-for-length <-2 Z			
	Abnormal infant development based on Ages & Stages Questionnaire (abnormal performance on ≥2 of the 7 domains)			

1 Hemoglobin determined during the third trimester, or by maternal questionnaire in Denmark.

2 Using a locally appropriate and validated FFQ.

MMN, multiple micronutrients; MUAC, midupper arm circumference.

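### The nonsupplemented label is wider than Table 3 allows: four reference nutrients may be supplemented, other supplement use is a listed exclusion only at visit 2, and the diet rows disagree

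*Protocol article*

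**What the plan says.** **The label.** The Abstract describes the participants as "Well-nourished, unsupplemented women in Bangladesh, Brazil, Denmark, and The Gambia". The Data analysis plan says the RVs will be expressed as percentiles "in these well-nourished, but nonsupplemented, population groups". Neither place gives an exception.

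**Permitted supplements.** In Table 3 (Inclusion criteria), the rows on multiple-micronutrient (MMN) use in the third trimester and in lactation permit "Iron and folic acid", in a cell that appears to span all four sites. They also permit "Vitamin D and calcium", which by column position applies to Denmark only.

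**Exclusions by visit.** The visit 2 list contains "Maternal MMN consumption during lactation other than stated above". The block headed "Visits 3 and 4 exclusion criteria" has three entries: stopping breastfeeding, low infant Z scores and abnormal development. Supplement use is not among them.

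**Diet.** For Bangladesh, Denmark and The Gambia the Table 3 criterion is "≥15 g of ≥15 food groups each/d". For Brazil it is "≥15 g of 4 of 8 food groups/d".

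**Removal from RV construction.** The Data analysis plan removes data on the basis of growth, development and nutritional status. Maternal supplement use is not named.

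**The concern.** The end of the Introduction makes reference ranges for milk vitamins and minerals the primary outcome. The Discussion intends them as benchmarks for judging milk quality and the effect of later nutrient interventions. For that use, the reader must know whether a centile describes women who did not take the nutrient or a mixture of users and non-users. As written, the label claims the first for every nutrient, while eligibility allows the second for iron, folate, vitamin D and calcium.

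The visit lists raise a second problem. If they are applied as printed, samples from a mother who starts another micronutrient product after visit 2 stay in the RV set. That would affect every nutrient in the product, not only the four permitted ones.

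The diet rows bear on the other half of the label, *well-nourished*. If sites qualified women by different standards, the pooled population has no single definition.

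**Working it through.** The plan states no figure on this point, so the check is mainly a comparison of passages. The arithmetic below is illustrative.

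**1. Are the permitted supplements RV nutrients?** Table 4 lists iron, calcium, folic acid and 5-methyl tetrahydrofolate, and the D2, D3 and 25-OH-D forms as milk analytes. Table 2 names a laboratory for milk vitamin D. Each permitted supplement therefore maps to a nutrient that receives an RV.

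**2. Which windows lack a listed supplement exclusion?** Visit 2 covers 1.0–3.49 mo, visit 3 covers 3.5–5.99 mo and visit 4 covers 6.0–8.5 mo. The exclusion appears for the first only. The uncovered span is 8.5 − 3.5 = 5.0 mo out of 8.5 − 1.0 = 7.5 mo, or two thirds of the curve. The lactation row of the inclusion criteria has no end date and could be read as running to 8.5 mo. The two parts of Table 3 therefore give different answers.

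**3. Diet rows.** A minimum of 15 groups cannot be met on an 8-group list. Either the sites count on different lists or one figure is misprinted. The text does not show which, nor that the two rules are comparable.

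**4. How far could the label mislead?** Assume a share *f* of the pooled women has milk values shifted up by *d* SD, with a normal distribution and equal SD. The pooled *p*-th centile *q* solves

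(1 − f)·Φ(q) + f·Φ(q − d) = p,

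and Φ(q) is its true position among unsupplemented women. Both *f* and *d* are assumptions, because the documents give neither.

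| f | d (SD) | Nominal 5th lies at | Nominal 50th lies at | Nominal 95th lies at |
|---|---|---|---|---|
| 0.25 | 0.1 / 0.3 / 0.5 | 5.2 / 5.7 / 6.0 | 51.0 / 53.0 / 54.9 | 95.3 / 95.9 / 96.5 |
| 0.50 | 0.1 / 0.3 / 0.5 | 5.5 / 6.5 / 7.4 | 52.0 / 56.0 / 59.9 | 95.5 / 96.5 / 97.4 |
| 1.00 | 0.1 / 0.3 / 0.5 | 6.1 / 8.9 / 12.6 | 54.0 / 61.8 / 69.1 | 95.9 / 97.4 / 98.4 |

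The first row fits, for example, one site of four in which every woman is a user. The last fits a supplement taken by all women at all sites. A shift common to all sites leaves no difference between sites, so the planned equivalence test cannot reveal it.

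**5. Could supplement use alone decide pooling?** The site-comparison threshold is 0.30 SD. With equal effect *d*, the mean difference between two sites is (f₁ − f₂)·d.

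- Iron and folic acid, assuming 25–50% users at every site and d up to 1.0: at most (0.50 − 0.25) × 1.0 = 0.25 SD, below the threshold.
- Vitamin D and calcium, Denmark only, with no users elsewhere: the difference is f·d. It reaches 0.30 SD at f = 0.30 if d = 1.0 (0.30 × 1.0), or at f = 0.60 if d = 0.5 (0.60 × 0.5).

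**6. What would RVs from non-users only cost?** The plan has 250 women per site and time period, and asks for 255 per time point to estimate the centiles. With an assumed 50% users, 250 × 0.5 = 125 non-users remain per site. With 25% users, 250 × 0.75 is about 187.

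**The case against.** The strongest reply is that the label is shorthand. The relevant Table 3 row concerns multiple micronutrients and openly lists the permitted products. Table 1 uses the same term and rules out such use for Danish participants. Read with these tables, *nonsupplemented* means no product beyond those listed. This stands in part: nothing is hidden, and the defect is an unqualified label. It does not remove the defect, because the document never defines the term that way and the RVs are meant to be used on their own as benchmarks.

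On visits 3 and 4, the undated lactation row is a fair counter-reading. A reader might infer that a mother who starts a supplement at month 4 is certainly kept. The documents do not support that. They support only that the visit list omits the rule and the inclusion row may contain it.

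A reader might also infer that supplement use can by itself decide which sites are pooled. Step 5 shows that this does not follow for iron and folic acid, which appear to be permitted everywhere, under the user range assumed there. It is possible only for Denmark-only vitamin D and calcium, at the shares shown. In that case the Data analysis plan already allows RVs per site or from two or three pooled sites.

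A third tempting step is to require RVs from non-users only. Table 1 shows some of these supplements as government mandates or recommendations at some sites, so non-users may be few, and step 6 shows the loss of precision. Likewise, a common diet filter in the analysis would conflict with Table 6, which places maternal dietary intake among the outcomes that do not enter RV construction.

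Finally, how permitted users enter the models may be set out in the full protocol or SAP. That is why the point rests on what the article states: a label, an exclusion list and two diet rows that do not agree.

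**Conclusion.** The point holds as a conflict in stated content with three parts.

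- The label is wrong without qualification for iron, folate, vitamin D and calcium.
- The exclusion for other supplements is stated for one of three RV windows and left ambiguous for the other two.
- The diet rows set different standards for *well-nourished* as printed.

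The size is unknown from the documents. Under assumed shifts of 0.1 to 0.5 SD, the nominal 5th centile would sit between the 5.2th and 6.0th centile of unsupplemented women if a quarter are users, and between the 6.1th and 12.6th if all are. These figures assume normality, equal SD and the same effect in every user. The effect could be nil for some of the four nutrients, since the documents report none.

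The reading of Table 3 by column position is likewise an inference from the layout. The documents do not establish that the RVs are invalid or that pooling would be decided by supplement use. The correction is worth making because it is cheap and determines what the published centiles describe.

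**What to change.** 1. **RV analysis set.** Apply the visit 2 supplement exclusion to visit 3 and 4 samples as well, and reconcile the Table 3 inclusion row and visit lists accordingly. Cost: a somewhat smaller n at those visits. It also relies on supplement use being recorded there, which the article's text does not confirm.
2. **Label.** Restrict *nonsupplemented* to nutrients other than iron, folate, vitamin D and calcium. State that the RVs for these four include permitted users. Where numbers allow, report user and non-user centiles as a sensitivity analysis; do not require non-user-only RVs. Cost: wording and one extra analysis for four nutrients, with wide intervals where either group is small.
3. **Diet criterion.** Reconcile the Table 3 diet rows, correcting a misprint if there is one or stating the food-group list behind each figure. Which threshold is right is for the investigators to say. Cost: wording only.
4. **Pooling.** No new rule is needed. When Danish vitamin D or calcium differs from the other sites, report the permitted use alongside the site comparison, so that the difference is not read as a population difference.
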